## Abstract

**Objectives:**

The primary aim is to compare the effects of backward walking exercise to forward walking exercise on knee pain, knee functions, and thigh muscle strength in individuals with mild to moderate knee osteoarthritis using lower body positive pressure, in addition to mobility functions, balance, and self-reported health status.

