**Methods:**

The study is a single blind randomized clinical trial with two independent groups. This study will enroll 26 participants with mild to moderate knee osteoarthritis. The participants will be randomized into either experimental group (backward walking exercise) or control group (forward walking exercise). Both groups will use lower body positive pressure treadmill for walking exercise. Both groups will perform regular conventional exercise and worm-up exercise before walking exercise. The treatment will be three times a week for six weeks. Walking session will be up to 30 min each session. Data collection will be collected during pre- and post- intervention including primary outcomes including numeric pain rating scale (NPRS), knee injury and osteoarthritis outcome score (KOOS), and thigh muscle strength test. The secondary outcomes include five times sit to stand test (FTSTS), 3-meter backward walk test (3MBWT), timed up and go test (TUG), four square step test (FSST), functional reach test (FRT), 10-meter walk test (10-MWT), six minute walk test (6MWT), medical outcomes study short form 12 (SF-12), patient health questionnaire -9 (PHQ-9), and rapid assessment of physical activity (RAPA). An independent t-test will be used to evaluate the effect of treatment on the outcome measures.

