**Conclusion:**

Using lower body positive pressure may have promising results against knee osteoarthritis. Moreover, walking backward exercise using lower body positive pressure might add more benefits to individuals with knee osteoarthritis and help clinicians in decision making.

*Trial registration*: This study was registered in ClinicalTrails.gov (ID: NCT05585099).

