##### Intervention

After signing the informed consent form, participants will fill out an intake form about demographic data and clinical variables. Additionally, they will be evaluated on inclusion/exclusion criteria. Participants meeting the inclusion criteria will be recruited in the study and assessed on the primary and secondary outcome measures. For test order, participants will be randomly assigned to one of four groups. A counterbalanced approach will be used to manage the order effects of learning and fatigue associated with the administered tests.

Participants will be randomized on the first day of the intervention to either a EG or CG. All participants will receive manual therapy and therapeutic exercise (Table 1) as described previously [12]. LBPP (AlterG Anti-Gravity Treadmill, Fremont, CA, USA) will be used for both forward and backward walking exercise (Fig. 3). All participants will have three sessions a week for 6 weeks (18 sessions) for up to 1 h/session. For the CG, gait training will be trained on forward walking using LBPP. The EG will be trained on backward walking using LBPP. For both groups, progression of gait training time will be instructed to gradually increase up to 30 min over the 6 weeks period. The air pressure inside chamber will be set to achieve pain free or max pain relief. Treadmill speed will be continuously assessed and increased gradually depending on the patient’s capacity. All participants will have 5 min of warm-up and cool-down exercise including heel raise, and hamstring and gastrocnemius-soleus stretches. All interventions and activities will be formed with a supervision of licensed physical therapists. Physical therapists will be trained on delivering the intervention and reporting the needed data each session. Before beginning the study, the evaluator will receive training on data collection and measuring all outcome measures.

**Table 1 Tab1:** Protocol exercise for all groups

Exercise	Procedure	Frequency	Intensity	Progression
Isometric quadriceps exercise	Patients lay in a supine position. A rolled-up towel was put beneath the knee. They were instructed to maximally activate their thigh muscles in order to straighten their knee and hold the contraction for 5 s	3 days/week	1 set of 10 repetitions/twice a day	1st week: 1 set 2–3 weeks: 2 sets 3–6 weeks: 3 sets

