### Statistical analysis

The collected data will be analyzed with IBM SPSS version 28.0 (IBM Corp., Armonk, NY, USA). The descriptive demographic data (means, medians, standard deviation, and frequencies) include age, gender, onset of knee OA, height, weight, knee involved, and all primary and secondary outcome measures will be computed and compared between two groups at the baseline using independent t-test. The Shapiro–Wilk test will be used to evaluate the normality assumption. A dependent *t*-test or Wilcoxon signed rank test will be performed to evaluates the difference between pre-intervention and post-intervention. The independent *t*-test or Mann–Whitney *U*-test will be performed to evaluate the difference between groups at the baseline and post-intervention. The level of significance will be set at *p* < 0.05.

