### Future directions and clinical implications

We have proposed a study protocol where knee pain in people diagnosed with OA is treated conservatively by walking exercise using LBPP. The primary goal of the study is to assess whether backward walking exercise using LBPP can alleviate knee pain symptoms in individuals diagnosed with OA. We believe that specific combinations of using a LBPP treadmill and doing backward exercises will relieve knee pain. As such, conservative treatment might be more cost-effective and have better outcomes than other treatments, such as surgical procedures.

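### Paired pre-post tests stand beside the between-group test with no descriptive label, and the closing statement of the primary goal omits the forward-walking comparator

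*Protocol article*

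**What the plan says.** **The question.** The abstract's Objectives are comparative: "The primary aim is to compare the effects of backward walking exercise to forward walking exercise on knee pain". The hypothesis at the end of the Introduction is comparative too: backward walking is expected to add benefit over forward walking, both on LBPP. The section Future directions and clinical implications puts it differently: "The primary goal of the study is to assess whether backward walking exercise using LBPP can alleviate knee pain symptoms". Forward walking is not mentioned there.

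**The analysis.** The Statistical analysis section lists a dependent t-test or "Wilcoxon signed rank test will be performed to evaluates the difference between pre-intervention and post-intervention". Next comes an independent t-test or Mann–Whitney test that "will be performed to evaluate the difference between groups at the baseline and post-intervention". One significance level, p < 0.05, closes the paragraph and covers everything in it. No test is marked as descriptive and none is ranked above another. The abstract's Methods are clearer: "An independent t-test will be used to evaluate the effect of treatment on the outcome measures".

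**The arms.** Under Intervention, the LBPP treadmill "will be used for both forward and backward walking exercise", and "All participants will receive manual therapy and therapeutic exercise". Table 1 gives one exercise programme for all groups. The arms differ in walking direction only.

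**The conclusion.** The abstract's Conclusion opens with "Using lower body positive pressure may have promising results against knee osteoarthritis". Its next sentence turns to what backward walking might add.

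**The concern.** A goal with no comparator invites an answer from change within the backward-walking arm, and the analysis section supplies a significance test that seems to give one. Two misreadings are then open. If both arms improve significantly, LBPP may get the credit although no arm goes without it. If only the backward arm reaches p < 0.05, this may be taken as superiority although the arms were not compared.

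The Introduction shows that the subject lends itself to this. It credits backward walking in an earlier six-week study with a larger fall in pain than forward walking, and then reports that the two did not differ significantly on any outcome.

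At stake is whether the trial's conclusion rests on the randomised comparison or on before-and-after change.

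**Working it through.** The plan gives no figure on this point, so there is none to reproduce. The check has two parts.

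**1. What each contrast can show**

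Write the mean change in each arm as a sum (additive for simplicity):

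- backward arm: L + M + E + N + B
- forward arm: L + M + E + N + F

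L is the effect of LBPP, M manual therapy and E the exercise programme (all shared, from Intervention and Table 1). N is regression to the mean plus natural course. B and F are the effects of walking direction.

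- A paired test in the backward arm tests L + M + E + N + B = 0. It cannot separate B or L from the rest.
- The between-arm difference is B − F. The shared terms cancel, and this is the question in the abstract and Introduction.
- No contrast in the design isolates L.

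N is unlikely to be zero. The Inclusion criteria require knee pain in the past 30 days, and in bilateral disease the most symptomatic knee is the one analysed. Both select on a high starting value.

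**2. How often one arm alone is significant when the arms do not differ**

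Inputs:

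- n per arm: 11 evaluable or 13 enrolled (Sample size calculation).
- Two-sided level: 0.05. The document gives p < 0.05; two-sided is assumed.
- dz = mean change / SD of change, the same in both arms. The document gives no value. Assumed range: 0.3 to 1.2.

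Formulas:

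- p = P(|T| > t(0.975; n−1)), where T is noncentral t with n−1 degrees of freedom and noncentrality dz·√n.
- The arms hold different participants, so the two tests are independent. P(exactly one significant) = 2p(1−p); P(both) = p².

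Example at n = 11, dz = 0.6: noncentrality = 0.6 × √11 = 1.99 and p = 0.436, so 2 × 0.436 × 0.564 = 0.492.

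| dz | n = 11: p | exactly one | both | n = 13: p | exactly one | both |
|---|---|---|---|---|---|---|
| 0.3 | 0.147 | 0.251 | 0.022 | 0.169 | 0.281 | 0.029 |
| 0.5 | 0.323 | 0.438 | 0.104 | 0.382 | 0.472 | 0.146 |
| 0.6 | 0.436 | 0.492 | 0.190 | 0.512 | 0.500 | 0.262 |
| 0.8 | 0.668 | 0.444 | 0.446 | 0.754 | 0.371 | 0.569 |
| 1.0 | 0.848 | 0.258 | 0.718 | 0.911 | 0.163 | 0.829 |
| 1.2 | 0.947 | 0.100 | 0.897 | 0.977 | 0.044 | 0.955 |

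By symmetry, half of the discordant results favour backward walking: at most 0.50 / 2 = 25%. A valid two-sided between-arm test at 0.05 would err in that direction 2.5% of the time.

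As the common change grows, discordance falls, but both arms are then usually significant: 90% (n = 11) or 96% (n = 13) at dz 1.2. That pattern invites the other misreading, credit to LBPP.

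**The case against.** The strongest reply is that the document never calls the paired tests tests of treatment effect. The analysis section says only that they assess the pre-post difference, and does not say that they are run per arm, although that is the likely reading. The abstract's Methods assign the treatment effect to the independent t-test, and the analysis section includes that comparison after the intervention. Nothing says that significance in one arm alone will count as superiority. **This stands.** A reader might infer that the plan makes the paired tests its efficacy tests; the text does not support that.

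A reader might also infer that the shared LBPP, manual therapy and exercise undermine the trial's main question. They do not, because they cancel in backward versus forward walking. **This stands too.**

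The sentence opening the abstract's Conclusion is hedged, precedes any results and is followed by a comparative sentence. The remark on cost-effectiveness and surgery in the closing section is equally hedged. These are editorial expectations and specify no analysis. The goal that lacks a comparator also sits in a closing section and replaces no stated objective.

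The probabilities depend on assumed changes and are small when the common change is large. If the paired test were run on both arms pooled, 2p(1−p) would not apply, though the pooled change would have no comparator either.

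What the reply does not remove: the analysis section applies one threshold to paired and between-group tests without distinguishing their roles, and the document words its primary goal in two ways, one of which the design cannot answer.

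**Conclusion.** The point holds as a matter of unclear roles and inconsistent wording. The paired tests lack a descriptive label, and the goal in the closing section does not match the comparative aim in the abstract and Introduction. Because both arms receive LBPP, manual therapy and the same exercises, pre-post change cannot show an effect of LBPP or an advantage of backward walking.

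If the arms truly change equally, exactly one is significant in up to about 50% of trials at 11 to 13 per arm for moderate changes (dz about 0.5 to 0.6). The figure is 25 to 28% at dz 0.3 and about 4 to 10% at dz 1.2. This assumes separate paired t-tests in each arm, two-sided 0.05, normally distributed changes and equal n; the Wilcoxon alternative was not computed. The defect itself does not depend on these figures, which only show how misleading the pattern can be.

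The between-arm comparison of walking direction remains valid in principle. Whether the sample is large enough for it is a separate matter on which this point does not rest.

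**What to change.** 1. **Statistical analysis.** Replace the paired tests by within-arm mean change with 95% CI, stated to be descriptive.
2. **Statistical analysis.** Carry over the rule from the abstract's Methods that the treatment effect is judged on the between-arm comparison. Specify it as the post-intervention difference between arms adjusted for the baseline value of the same outcome (ANCOVA), with 95% CI. State that significance in one arm and not the other is not evidence of superiority.
3. **Future directions and clinical implications.** Reword the goal as a comparison of backward with forward walking on LBPP, in line with the abstract and Introduction.
4. **Reporting.** Draw no conclusion about LBPP itself from this trial.

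**Cost.** Within-arm p-values are given up. Items 1, 3 and 4 are wording. Item 2 changes the between-group analysis by one covariate, already collected at T0. It uses one degree of freedom (22 − 2 = 20 becomes 22 − 3 = 19 with 11 per arm) and needs no further participants, visits or measurements.

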## Materials and methods

### Study design

This study is a prospective two-arm single-blinded RCT. The experimental group (EG) will perform backward walking exercise, and the control group (CG) will perform forward walking exercise using LBPP device. All outcome measures will be collected at baseline (T0) and post-intervention following 6 weeks or 18th session (T1) (Fig. 1).

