##### Sample size calculation

G Power software analysis version 3.1.9.2 (University of Kiel, Kiel, Germany) was used to determine the sample size using pain level changes following intervention from a prior study [12]. With a small effect size of 0.29, *α* level of 0.05, and power of 0.80, the required sample size is 22 participants (11 participants per group). With a 20% attrition rate, there will be a total of 26 participants for total sample (13 participants in each group).

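### The between-group analysis compares unadjusted post-intervention scores although every outcome has a baseline value; ANCOVA on baseline would gain precision at almost no cost

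*Protocol article*

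**What the plan says.** The article fixes the analysis in two places.

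- **Abstract, Methods:** "An independent t-test will be used to evaluate the effect of treatment on the outcome measures".
- **Statistical analysis:** the independent t-test or the Mann-Whitney U-test "will be performed to evaluate the difference between groups at the baseline and post-intervention".

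Baseline values are available throughout. Under Study design: "All outcome measures will be collected at baseline (T0) and post-intervention". The Statistical analysis section uses them in two ways. One is a pre/post test, where a dependent t-test or Wilcoxon "signed rank test will be performed to evaluates the difference between pre-intervention and post-intervention". The other is a comparison of the arms before treatment: "all primary and secondary outcome measures will be computed and compared between two groups at the baseline using independent t-test". Neither estimates the difference between backward and forward walking after treatment. No between-group analysis uses change from baseline or a baseline covariate.

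On the choice between the parametric and the rank test, the section says "The Shapiro–Wilk test will be used to evaluate the normality assumption". It gives no other rule, so the normality test appears to decide.

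**The concern.** With 13 randomised per arm, and 11 per arm if attrition is as planned, the arms can differ noticeably at T0 by chance. Where T0 and T1 scores are correlated, part of that gap carries into the T1 difference. A baseline test does not remove it. It only reports it, and the article states no action if the arms differ.

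The loss grows with the T0-T1 correlation. Peak torque in a mixed sample of men and women is an outcome where stable differences between people could be large, though the article gives no correlation for any measure. In a trial this small, baseline adjustment is precision already paid for, because the T0 assessment is done anyway.

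The normality test raises a lesser issue. The reported effect could be a mean difference for one outcome and a rank comparison for the next, depending on the data. The rank branch yields no mean difference to set against the 1 to 1.7 point minimal important difference that the article quotes for the NPRS.

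**Working it through.** **Inputs.** From the article: 13 per arm randomised, 11 per arm after attrition, α = 0.05 (taken as two-sided), effect size 0.29 (metric not stated). Assumed: T0-T1 correlation r = 0.3, 0.5 or 0.7, equal SDs at T0 and T1, normal data, and an illustrative true effect d = 1.0 SD. The article supports neither r nor d = 1.0; they only show scale.

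**1. Chance baseline gap.** SD of the difference in T0 means, in outcome SDs = √(2/n).
- n = 13: √(2/13) = 0.392. P(|gap| > 0.5) = 2 × [1 − Φ(0.5/0.392)] = 2 × [1 − Φ(1.275)] = 0.20.
- n = 11: √(2/11) = 0.426, and the same probability is 0.24.

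A gap of one such SD moves the expected post-only difference by r × 0.392 at 13 per arm: 0.12, 0.20 or 0.27 SD at r = 0.3, 0.5 or 0.7.

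**2. Variance relative to the post-only comparison.** ANCOVA: 1 − r². Change score: 2(1 − r). Equivalent post-only size at 11 per arm: 11/(1 − r²).

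| r | ANCOVA | Change score | Equivalent n per arm |
|---|---|---|---|
| 0.3 | 0.91 | 1.40 | 12.1 |
| 0.5 | 0.75 | 1.00 | 14.7 |
| 0.7 | 0.51 | 0.60 | 21.6 |

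A change-score test is worse than the planned test at r = 0.3 and equal to it at r = 0.5, so it is not the remedy.

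**3. Power at 11 per arm.**
- Post-only: non-central t with 20 df and non-centrality d√(11/2).
- ANCOVA: 19 df and non-centrality d√(11/2) / √[(1 − r²) × k]. The factor k = 1 + 1/(2n − 4) = 1 + 1/18 = 1.056 allows for estimating the covariate slope in 22 people.

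| True effect | Post-only | ANCOVA r = 0.3 | r = 0.5 | r = 0.7 |
|---|---|---|---|---|
| d = 1.0 (assumed) | 61% | 62% | 71% | 86% |
| d = 0.29 (article's figure read as d) | 9.9% | 10.1% | 11.2% | 14.2% |

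Leaving out k would give 73% and 88% at d = 1.0 for r = 0.5 and 0.7, slightly too favourable. Simulating the fitted ANCOVA at d = 1.0 agrees with the table to within about one percentage point.

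**4. Validity of the planned test.** Two-arm normal data with no effect, 11 per arm, were simulated 4,000 times at each r. The type I error was 4.3% to 5.7% across the Shapiro-Wilk-gated post-only test, the change-score test and ANCOVA. The gate did not inflate the error.

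**The case against.** The strongest reply is that nothing here is invalid. Under randomisation a post-only comparison is unbiased, its standard error already allows for chance imbalance, and its type I error is at the nominal level. That stands in full. A reader might infer from the baseline-gap figures that the planned estimate is biased, but the article does not support that. The estimate depends on the gap that occurs in this one trial, and is less precise than it could be.

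The gain also depends on a correlation that the article does not give. At r = 0.3 it is one percentage point of power at d = 1.0. That stands too, and is why a range is shown.

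Three stronger readings are tempting and should be resisted.

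- **That baseline is ignored altogether.** It is used in the pre/post tests and the baseline comparison; it is absent only from the between-group estimate.
- **That the analysis tests a different quantity from the one the trial was sized on.** The sample size was set "using pain level changes following intervention from a prior study", which hints at a mismatch with T1 scores. But the section states neither the test family nor whether 0.29 is a between-arm contrast of changes, so the mismatch cannot be established.
- **That the normality gate makes the primary test unsound.** No error inflation was found with normal data, and bounded or discrete scales such as the NPRS and PHQ-9 give some reason to keep a rank method available. What remains is that the form of the reported effect should not be left to the data.

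**Conclusion.** The point holds as an efficiency improvement that should be made, not as a flaw that invalidates the trial. The article itself fixes the unadjusted comparison, in the abstract and again in the Statistical analysis section, so this is not a detail left to an analysis plan that is not shown.

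Baseline adjustment would cut the variance by 9%, 25% or 49% at r = 0.3, 0.5 or 0.7. It is negligible at the low end and worth nearly twice the patients at the high end. These figures rest on the assumed correlations and on roughly normal outcomes.

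A reader might infer that ANCOVA would bring the trial to its stated 80% power. It would not. If 0.29 is a standardised mean difference, power at 11 per arm stays at about 10% to 14% either way. The sample size is a separate question. The Shapiro-Wilk issue is secondary.

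**What to change.** In the Statistical analysis section, and in the abstract to match:

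1. Make the between-group analysis of each continuous outcome an ANCOVA of the T1 score on group and the T0 score of the same measure.
2. Report the adjusted mean difference with its 95% CI.
3. Let the normality test no longer choose the primary analysis. Name one rank-based sensitivity analysis in advance, such as a rank or permutation ANCOVA, and report it whatever the normality test shows.

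The change should be made before anyone sees outcome data by arm, so that the choice to adjust cannot be driven by results.

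The cost is a change of wording. T0 is already collected and the named software fits the model. The statistical cost is one residual degree of freedom plus about 6% of variance for estimating the slope at 11 per arm (k = 1.056). At r = 0.3 the 9% reduction still slightly outweighs this: 0.91 × 1.056 = 0.96. If the correlation were near zero, adjustment would lose a little.

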### Ethics statement and consent to participate

The studies involving human participants were reviewed and approved by the National Bioethics Committee Review Boards. The patients/participants will be provided a written informed consent to participate in this study.

